### **Sample size assessment**

Sample size calculation was based on the following conditions:

2 points reduction on a numerical pain scale of 0-10, for the patient experiencing a reduction in pain as clinically important.

- The Average highest pain at baseline is 5.8 and SD = 3 (3; 35). –A total of 70% of all pregnant women who experience low back pain.
- We assume that the effect of the intervention is 2.0 points if all participants complete the full program.
- It is estimated that 50% of participants follow the program for at least 75% of the sessions (high participation, 19-24 sessions) while 35% follow 50-75% (moderate participation, 12 - 18 sessions) and 15% follow less than half of the program (low participation). We estimate that the effect of high participation in the training course is a reduction of 2 points, the effect of moderate participation in the training course is a reduction of 1 point, while low participation does not result in a reduction. This gives an overall reduction in the intervention group of 1.35 points ( $0.50 * 2 + 0.35 * 1 + 0.15 * 0 = 1.35$ ). A difference in pain level of 1.35 (SD = 3.0) will be available with a power of 90% and a significance level of 5% (two-sided) with 150 participants in each group.

[figure not shown]

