### **General statistical considerations**

The primary data analysis will be performed based on the intention-to-treat principle.

Baseline data (parity, previous low back pain) for the two groups will be compared: For quantitative data a t-test will be applied if the data are sufficiently normal, otherwise the Kruskal-Wallis test will be applied. Qualitative data will be compared by the Fisher or chi-square test, the latter being applied if the condition of the expected values being larger than 5 is fulfilled.

A t-test will be applied to compare the mean of the primary outcome in the two groups. Similarly secondary outcomes will be compared using t-tests. For the secondary outcomes, the p-values will be adjusted for multiple testing using the Benjamini-Hochberg correction method (ref). If the data are not sufficiently normally distributed, a transformation will be applied if possible.

To explore the impact of parity and previous low back pain score on the outcomes, additional linear regression analyses of the outcomes will be performed. In case of influential observations (probably only relevant for number of days on sick leave), robust regression techniques will be applied. Per- protocol analysis will be performed of the pregnant women who perform  $\geq 75\%$  of all training sessions. The significance level will set at 0.05.

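### The stated 90% power at 150 per group does not match the planned intention-to-treat comparison: 97% if the 1.35-point effect applies to all women, about 78% or less if only to the 70% with pain

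*Protocol*

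**What the plan says.** The section Sample size assessment lists the conditions behind the calculation. Worst pain at baseline is given as "The Average highest pain at baseline is 5.8 and SD = 3". The next condition is the share of women affected: "A total of 70% of all pregnant women who experience low back pain". The section does not say how that share is used. It then weights assumed effects of 2, 1 and 0 points by expected attendance of 50%, 35% and 15%: "This gives an overall reduction in the intervention group of 1.35 points". The conclusion is: "A difference in pain level of 1.35 (SD = 3.0) will be available with a power of 90" per cent, at a two-sided 5% level, "with 150 participants in each group".

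Four other places bear on this:
- The inclusion criteria (section Participants) do not ask for low back pain.
- General statistical considerations says: "The primary data analysis will be performed based on the intention-to-treat principle", and sets a t-test between the two groups for the primary outcome.
- The Dropout section expects a 25% loss.
- The Time schedule plans to include 550 women.

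**The concern.** The power sentence names four inputs (difference, SD, significance level, group size), and these do not give the power it states. The listed 70% leads back to 150, but dividing by 0.70 treats the other 30% as women who drop out of the comparison. In an intention-to-treat t-test they stay in both group means. If they have no effect, they shrink the difference itself, and the required number then grows by about 1/0.70² = 2.04, not by 1/0.70 = 1.43.

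At stake is how a null or borderline primary result would be read. A reader relying on 90% could take a null result as stronger evidence against the programme than the design supports. The error could also run the other way, with the plan conservative. The text does not let a reader tell which.

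**Working it through.** **Inputs.** Difference δ = 1.35, SD σ = 3.0, two-sided 5%, power 90%, n = 150 per group, 70% with pain and baseline worst pain 5.8 (all from Sample size assessment); allocation 1:1 (Design); 25% dropout (Dropout); 550 included (Time schedule).

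**1. The sentence as written.** n per group = 2(z₀.₉₇₅ + z₀.₉₀)²σ²/δ² = 2 × (1.960 + 1.282)² × 9 / 1.8225 ≈ 104. The exact t-test calculation (noncentral t) gives 105. At n = 150 the standardised difference is 1.35 / (3.0 × √(2/150)) = 3.90, and power is 97.3%. The sentence alone does not reproduce 90%.

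**2. Finding the 150.** A one-sided 5% test needs 85, 95% power needs 129, and inflating 104 for 25% dropout gives 104/0.75 = 139. None of these is 150. Using the 70%, 105/0.70 = 150. Equivalently, 150 × 0.70 = 105 women with pain per group, whose comparison has 90.1% power. This is the only route I found that reproduces the plan's figure.

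**3. The planned intention-to-treat comparison, 150 analysed per group.**

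- *Reading A: 1.35 is the mean effect over all participants.* Power is 97.3%, as in step 1.
- *Reading B: 1.35 applies to the 70% with pain, and the other 30% have no effect (assumption).* The difference is 0.70 × 1.35 = 0.945. With SD 3.0 the standardised difference is 0.945 / (3.0 × √(2/150)) = 2.73, and power is 77.6%.
- *Reading C: as B, and in addition 5.8 and SD 3.0 describe only women with pain while the rest score 0 (assumptions).* Control-arm variance is 0.70 × 9 + 0.70 × 0.30 × 5.8² = 13.36 (SD 3.66). In the intervention arm, women with pain average 5.8 − 1.35 = 4.45, so the variance is 0.70 × 9 + 0.70 × 0.30 × 4.45² = 10.46 (SD 3.23). The pooled SD is √((13.36 + 10.46)/2) = 3.45, and power is 65.7%.

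For 90% power, reading B needs 213 analysed per group and reading C needs 282.

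**4. At the recruitment target.** 550/2 = 275 per group; 275 × 0.75 ≈ 206 analysed per group.

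| Reading | Difference / SD | Power, 150 analysed per group | Power, 206 analysed per group |
|---|---|---|---|
| A | 1.35 / 3.0 | 97% | over 99% |
| B | 0.945 / 3.0 | 78% | 89% |
| C | 0.945 / 3.45 | 66% | 79% |

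**The case against.** The strongest reply is that nothing was miscalculated. The 70% is among the listed conditions, and with it 150 and 90% come out exactly. That stands: the fault is not that the figure cannot be derived, but that the derivation powers a different comparison from the planned one.

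Second, the dilution to 0.945 is not in the protocol. The 1.35 is described as a reduction across the intervention group, and the introduction speaks of preventing pain as well as reducing it, so women without pain at entry might benefit. The section also does not say whether the 70% means pain at entry or at any time in pregnancy. This stands too, and is why 0.945 is only one reading. It does not rescue the 90%. With SD 3.0 and 150 per group, 90% corresponds to a difference of about 3.24 × 3.0 × √(2/150) = 1.12, and the protocol derives no such intermediate value.

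Third, a reader might infer that the trial is underpowered. The documents do not support that as a general statement. With 550 included and 25% lost, even the diluted difference has about 89% power at SD 3.0; only the further assumptions of reading C bring it to about 79%. Applying the control-arm SD of 3.66 to both arms would give lower figures still (about 61% at 150 and 74% at 206), but that overstates the spread in the intervention arm.

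Finally, a figure follows the power sentence that I could not see. It may explain the step from 300 to 550, so the absence of that step from the text is a lesser point.

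**Conclusion.** The power statement is wrong for the analysis the protocol plans. That 1.35 with SD 3.0 gives 97% at 150 per group, and needs 105 for 90%, rests on the protocol's own figures alone. That 150 came from 105/0.70 is an inference, but the match is exact and the alternatives tried fail.

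The size and direction of the error depend on who the 1.35 describes: 97% if all participants, about 78% if only women with pain and the rest have no effect, and about 66% if pain-free women also score 0. None of these three readings gives 90% at 150 analysed per group. The recruitment target of 550 may largely make up any shortfall, so the conclusion concerns a misstated power figure and an undefined target population. It does not show that the trial is too small.

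**What to change.** Rewrite the sample size paragraph so that it:

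1. says whether 1.35 and SD 3.0 describe all randomised women or only those with low back pain, and whether the 70% means pain at entry or at any time in pregnancy;
2. shows how the 70% and the 25% dropout enter the calculation. If 105 is kept, it should be labelled as the number of women with pain analysed per group for 90% power;
3. reconciles the 300 women of this section with the 550 of the Time schedule;
4. replaces the 90% with the power of the intention-to-treat comparison at the planned number. At about 206 analysed per group this is over 99% if 1.35 applies to all, about 89% for 0.945 at SD 3.0, and about 79% for 0.945 at SD 3.45. If the population behind 1.35 cannot be settled, give the range.

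The change is to text only and needs no extra enrolment. Its cost is that the stated power may be less favourable.

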### Strategy in case of missing outcomes

For outcomes with less than 5 percent missing data, complete case analyses will be reported. If the percentage of missing data exceeds 5, a sensitivity analysis based on worst-best and best-worst imputation will be applied (in the experimental arm imputing the worst / best outcomes observed in the control arm to the missing outcomes and vice versa for the control arm). In case these analyses give rise to the same conclusion as the complete case analyses, the latter will be reported. Otherwise data will be assumed Missing At Random (MAR) and analyses will be performed using Maximum-Likelihood or Inverse Probability Weighting.

| Primary outcome                        | Description                                                                                                                                                                                         | Handling of partly missing outcomes                                                            |
|----------------------------------------|-----------------------------------------------------------------------------------------------------------------------------------------------------------------------------------------------------|------------------------------------------------------------------------------------------------|
| Low back pain                          | Three numeric 11 point box scales (pain now, worst pain in the past two weeks, average pain in the past two weeks), 0 indicating no pain to 10 indicating worst pain imaginable.                    |                                                                                                |
| Secondary outcome                      |                                                                                                                                                                                                     |                                                                                                |
| Days spend on sick leave               | Number of days spend on leak leave,

1. Due to pregnancy-related complications.

2. Sickness or conditions with no relation to the pregnancy.

3. Due to the work environment.    |                                                                                                |
| Roland Morris Disability Questionnaire | A 23 item disease specific instrument developed to asses physical disability caused by low back pain.

Conversion of yes/no answers to a 0-100 scale. The answers is converted to percentages | When two answers ore more are missing the raw sum score will also be converted to percentages. |
| EQ-5D + termometer                     | General health status covering the five dimensions; mobility, self-care, usual activities, pain/discomfort and                                                                                      |                                                                                                |

|  |                                                                                                                                                                                                                                   |  |
|--|-----------------------------------------------------------------------------------------------------------------------------------------------------------------------------------------------------------------------------------|--|
|  | 
anxiety/depression. The five dimensions are each assessed by a single answer on a three-point ordinal scale (no problems, some problems, extreme problems).
 
Self-rated quality of life rated on a 0-100 point scale
 |  |
|--|-----------------------------------------------------------------------------------------------------------------------------------------------------------------------------------------------------------------------------------|--|

### **Recruitment of participants.**

Participants in the study will be healthy pregnant women who follow the antenatal care at Rigshospitalet, Copenhagen Denmark. As part of the antenatal care pregnant women fill out a standard questionnaire regarding health, previous pregnancies and lifestyle for the use in the antenatal care. Based on this information, participants will be selected for the study. The first contact to the participant is made by letter, containing written information about the trial. After one week the women will be contacted by a research midwife and invited to a face-to face meeting, if the woman is interested in hearing more about the trial.

At the meeting, which is held at Rigshospitalet in 16-17 weeks, the woman will receive oral information about the trial by a the research midwife. The conversation takes place in an enclosed space and the woman will get up to 30 minutes of second to decide whether she will participate in the trial. This reflection is considered acceptable when the woman already has had the opportunity to consider its participation. During the conversation in 16-17 weeks of pregnancy will obtain consent.

### **Dropout**

Women with Pelvic girdle syndrome are excluded from the trial. If Pelvic girdle syndrome is suspected, the women will have a physical examination by research midwife, trained by physiotherapist PhD [name], to exclude women with Pelvic girdle syndrome. If in doubt, the woman will be examined by a physiotherapist, committed to the project. The dropout rate in the intervention group is expected to be modest, with only 5% of all pregnant women diagnosed with Pelvic girdle syndrome. When pain occurs early in pregnancy around pregnancy week 20, and therefore will be diagnosed at baseline, there will be only 1-2% will develop pain after inclusion in the trial. Furthermore a dropout rate of 23% of participants due to other complications: 10% of pre-term birth or picking pangs 5% that gets hypertensive complications, and 13% to other complications ( vomiting, placenta praevia, stress, bleeding ect.). A total dropout rate of 25% due to pregnancy-related complications is expected.

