While the explanation for low back pain during pregnancy can be attributed to some muscle groups are more relax while others become more tense as a result of a change partly to the body's center of gravity and a woman's weight (34), it is obvious that physical activities, especially physical activities in water, which gives the pregnant woman a greater ability to move (23) may reduce the intensity of low back pain. It is important to distinguish between low back pain, and pelvic girdle syndrome, as the prognosis and the treatment is different (39). Pelvic girdle syndrome occurs in approximately 5% of pregnant women in Denmark, usually occurs around week 20 and gradually worsened during pregnancy (40). Pelvic girdle syndrome is defined as pain localized to the 3 sacroiliac joint. The prognosis for pelvic girdle syndrome is worse than for low back pain, as about 20% is still not free of pain two years after birth (41). Pelvic girdle syndrome is diagnosed by a physiotherapist, performing an examination of joints and muscles of the pelvic region, to ensure that the pain is joint- related and not muscular.

The evidence on the prevention and reduction of low back pain during pregnancy is very limited. Two Swedish studies found positive effects of exercise in water during pregnancy on low back pain, pelvic pain and sick leave (14; 35). A weakness in one study was that there were included women with both low back pain and pelvic pain (14). As the two syndromes have different etiology, treatment and prognosis, it may be misleading to assess the effect as a whole. Neither of the two studies described the intervention in details, which is necessary if the studies, is to be reproduced. In both studies the training took place at specific time, during daytime, and participants indicated having difficulty to follow a specific team. In one study the water training (intervention) took place in hot water (35), such a study is not possible to appliqué in Denmark as hot pools only exist in a limited number in Denmark.

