### **Indications for treatment stops**

- PPROM (Rupture of membranes before the 37th week of pregnancy)
- Symptomatic placenta praevia
- Pelvic girdle syndrome, diagnosed by a physiotherapist from international guidelines
- Vaginal Bleeding
- Threatening premature birth
- Preeclampsia

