### **Data Collection**

All information regarding participants is protected by law concerning the processing of personal data and Law about patients' legal position.

Background Data: Prior to randomization collected information about the woman's socio-demographic characteristics, height and weight, lifestyle factors (smoking, exercise, alcohol.),

Abuse and medical, gynecological and obstetric history, incl. fertility treatment, previous preterm birth and previous pelvic instability diagnosed by a physical therapist or doctor. This information is collected as part of the general systematic collection of medical records, which were held in Obstetric Clinic at Rigshospitalet.

Data on the current pregnancy and delivery: For all participants gathered information about complications in pregnancy and during labor, gestational age at birth, the children's weight and length at birth, and children's condition immediately after birth. These data are collected by chart review after birth. Information on low back pain and sick leave: Information collected in a questionnaire handed out at baseline in 16-17 weeks of pregnancy and sent to the participating women at follow up in the 32nd week of pregnancy.

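### The dropout estimate assumes that a condition arising around week 20 is diagnosed at a week 16–17 baseline, and exclusion for it is not limited to before randomisation

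*Protocol*

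**What the plan says.** **Timing.** The protocol's Background says that pelvic girdle syndrome "usually occurs around week 20 and gradually worsened during pregnancy", and gives a frequency of about 5% among pregnant women in Denmark. Women enter at 14–17 weeks (Participants) and consent at 16–17 weeks (Recruitment of participants). For low back pain and sick leave, Data Collection has: "Information collected in a questionnaire handed out at baseline in 16-17 weeks of pregnancy".

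**Dropout estimate.** The Dropout section reasons: "When pain occurs early in pregnancy around pregnancy week 20, and therefore will be diagnosed at baseline, there will be only 1-2" per cent who develop the pain after inclusion. It adds 23% for other complications, broken down as "10% of pre-term birth or picking pangs 5% that gets hypertensive complications, and 13% to other complications", and arrives at a total of 25%.

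**What happens to affected women.** Dropout states: "Women with Pelvic girdle syndrome are excluded from the trial". The exclusion criteria under Participants name the syndrome only in earlier pregnancies. Indications for treatment stops lists "Pelvic girdle syndrome, diagnosed by a physiotherapist from international guidelines". General statistical considerations says: "The primary data analysis will be performed based on the intention-to-treat principle". On absent outcomes, Strategy in case of missing outcomes says: "If the percentage of missing data exceeds 5, a sensitivity analysis based on worst-best and best-worst imputation will be applied".

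**The concern.** There are two linked problems.

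First, a condition that usually starts around week 20 cannot be assumed to be visible three to four weeks earlier. The 1–2% rests on that assumption alone, and the 25% total rests in part on the 1–2%. The 23% component also disagrees with its own listed parts.

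Second, the exclusion sentence has no time limit, stands under a heading about dropout, and shares a paragraph with women who fall ill after inclusion. It can therefore be read as taking randomised women out of the trial. The syndrome is a pain condition and the primary outcome is the intensity of low back pain at week 32. On that reading, membership of the analysed set would depend on something that happens after randomisation and is related to the outcome. Intention-to-treat is meant to prevent this.

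**Working it through.** **1. Timing.** Usual onset is about week 20 (Background, Dropout) and baseline is weeks 16–17 (Data Collection). 20 − 17 = 3 and 20 − 16 = 4, so usual onset falls 3–4 weeks after baseline. Diagnosis at baseline does not follow.

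**2. What 1–2% implies.** If 5% are affected overall and 1–2% arise after inclusion, the share already present at baseline is (5 − 2)/5 = 60% to (5 − 1)/5 = 80%. The protocol offers nothing to support that share. It gives no onset distribution either, so the share arising later is bounded only by the 5%. Of 550 women (Time schedule):
- 1–2%: 5.5 to 11 women
- 5%: 27.5 women

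The 5% is a ceiling. It describes all pregnant women, whereas the trial excludes those who had the syndrome in an earlier pregnancy, and some cases may be present at baseline.

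**3. The stated total.** 23% + 2% = 25%, so the plan's figure reproduces at the upper end of 1–2%. But 10% + 5% + 13% = 28%, not 23%. The 23% can stand only if some women have more than one complication, which the protocol does not say.

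**4. Restated totals**, adding the components as the protocol does:

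| Other complications | Syndrome after inclusion | Total dropout | Left of 550 | Left per arm of 275 |
|---|---|---|---|---|
| 23% | 1–2% (as stated) | 24–25% | 418–412.5 | 209–206 |
| 23% | up to 5% | up to 28% | 396 | 198 |
| 28% (no overlap) | up to 5% | up to 33% | 368.5 | 184 |

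The plan needs 150 per group, 300 in all. Enrolment per arm needed to keep 150 is 150/0.75 = 200, 150/0.72 = 209 and 150/0.67 = 224. All are below 275.

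**5. Exclusion wording, sections side by side.**
- Participants: no criterion covers the syndrome in the current pregnancy.
- Indications for treatment stops: a diagnosis stops training and nothing more.
- General statistical considerations: intention-to-treat for the primary analysis.
- Dropout: exclusion from the trial, with no time limit, in a paragraph that also counts cases after inclusion.

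The last is at odds with the middle two unless it is confined to the time before randomisation.

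**6. Effect on the missing-outcome bounds, if these women have no week-32 score.** Assume that a share p is missing in each arm and that observed scores span 0–10. The worst-best and best-worst results are then (1 − p) × observed difference ± 10p. At the stated 25% dropout, if all those outcomes are missing, 10p = 2.5 points. At 28% it is 2.8. The timing error adds about 0.3 to a bound that is already wide.

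**The case against.** The strongest reply is that the exclusion sentence describes screening. The next sentence has a research midwife examine women on suspicion in order to exclude the syndrome, and the paragraph then speaks of diagnosis at baseline. Later cases appear only as a forecast, introduced as dropout in the intervention group. Most other listed causes resemble the treatment-stop list, so dropout may simply mean stopping training. With intention-to-treat stated, treatment stops kept separate and the week-32 questionnaire sent to participants, the protocol may intend exactly what is right. Detailed analysis-set rules may also be in a statistical analysis plan that is not shown. This is a fair reading, so the second part is only an ambiguity. It remains worth fixing because no eligibility criterion carries the screening rule, and the sentence as written sets no limit in time.

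A reader might infer more, in three ways that the documents do not support.

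- **That the result will be biased in favour of exercise.** That would need more high-pain women to be removed from the exercise arm. Examination happens on suspicion. The intervention arm has more contact with staff (monthly sessions with a midwife or physiotherapist, weekly messages from the project midwife) than controls in standard care. Unequal detection is plausible but not shown. With equal removal the bias would be near zero.
- **That the trial is too small.** Even at 33% dropout, about 369 women remain against 300.
- **That these women alone would dominate the imputation bounds.** The other expected dropout, if missing, already produces most of the ±2.5 points.

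It would also go too far to say that the full 5% will arise after randomisation. The protocol gives a usual onset, not a distribution.

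**Conclusion.** The inference from onset around week 20 to diagnosis at weeks 16–17 contradicts the protocol's own timing, and the 1–2% has no other support. The 23% does not match its listed parts unless complications overlap. The stated 25% is therefore not supported as written: it could be up to 28% if 23% stands, or up to 33% without overlap. These limits assume that the protocol's 5% is a ceiling for the enrolled women and that components add. No sample-size or recruitment decision changes.

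The untimed exclusion is an ambiguity at odds with the treatment-stop rule and intention-to-treat. It could permit removal of randomised women for a condition related to the primary outcome, but the documents fix neither the size nor the direction of any bias. Overall the point is minor: a wrong inference and a loose sentence, both curable by wording.

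**What to change.** - In Dropout, limit exclusion to a diagnosis made before randomisation, and add current pelvic girdle syndrome to the exclusion criteria under Participants.
- State that a woman diagnosed later stops training, completes the week-32 questionnaire and is analysed as randomised.
- Use the same trigger for examination in both arms.
- Replace 1–2% by up to 5%, and either explain the overlap behind 23% or restate it as 28%, with the total to match.

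**Cost.** These are wording changes, and the week-32 questionnaire is already part of the plan. The downside is slight dilution from keeping women who stop training. A woman who starts at weeks 16–17 and stops around week 20 has done at most 3–4 weeks × 2 = 6–8 of 24 sessions (25–33%). She falls in the 15% low-participation group that the sample size assessment already credits with no effect. If the 15% covers such women, the planned 1.35 is unchanged.

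If 5% come on top, the difference is 1.35 × 0.95 = 1.28. Power (two-sided 5%, SD 3.0, normal approximation) then depends on how the 150 per group is read. The plain formula needs about 105 per group, and 105/0.70 = 150 if the 70% with low back pain is taken as a divisor, which the protocol does not state.
- All 150 count: 97.4% falls to 95.9%.
- Only 105 count: 90.3% falls to 87.2%.
- On the second reading with 550 enrolled and 28% lost, 275 × 0.72 × 0.70 = 138.6 per group, and power is 94.5%.
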